## Abstract

**Background:**

Health-system policy makers need timely access to synthesised research evidence to inform the policy-making process. No efforts to address this need have been evaluated using an experimental quantitative design. We developed an evidence service that draws inputs from Health Systems Evidence, which is a database of policy-relevant systematic reviews. The reviews have been (a) categorised by topic and type of review; (b) coded by the last year searches for studies were conducted and by the countries in which included studies were conducted; (c) rated for quality; and (d) linked to available user-friendly summaries, scientific abstracts, and full-text reports. Our goal is to evaluate whether a "full-serve" evidence service increases the use of synthesized research evidence by policy analysts and advisors in the Ontario Ministry of Health and Long-Term Care (MOHLTC) as compared to a "self-serve" evidence service.

**Methods/design:**

We will conduct a two-arm randomized controlled trial (RCT), along with a follow-up qualitative process study in order to explore the findings in greater depth. For the RCT, all policy analysts and policy advisors (n = 168) in a single division of the MOHLTC will be invited to participate. Using a stratified randomized design, participants will be randomized to receive either the "full-serve" evidence service (database access, monthly e-mail alerts, and full-text article availability) or the "self-serve" evidence service (database access only). The trial duration will be ten months (two-month baseline period, six-month intervention period, and two month cross-over period). The primary outcome will be the mean number of site visits/month/user between baseline and the end of the intervention period. The secondary outcome will be participants' intention to use research evidence. For the qualitative study, 15 participants from each trial arm (n = 30) will be purposively sampled. One-on-one semi-structured interviews will be conducted by telephone on their views about and their experiences with the evidence service they received, how helpful it was in their work, why it was helpful (or not helpful), what aspects were most and least helpful and why, and recommendations for next steps.

**Discussion:**

To our knowledge, this will be the first RCT to evaluate the effects of an evidence service specifically designed to support health-system policy makers in finding and using research evidence.

**Trial registration:**

ClinicalTrials.gov: NCT01307228

## Background

Health-system policy makers make important decisions every day about the governance, financial, and delivery arrangements within which programs, services, and drugs are provided and about implementation strategies [1]. The nature of their decisions will vary according to the setting in which they work (*e.g.*, federal, provincial, or local government) and the role they play (*e.g.*, political staff, policy analyst, senior policy advisor, Assistant Deputy Minister, or elected official), among other factors. Systematic reviews are increasingly seen as a key source of information to inform these decisions [1]. Reduced bias and increased precision comprise the main advantages of systematic reviews that address questions about the effects of interventions [2]. Drawing on a systematic review that addresses *any *question constitutes a more efficient use of time for busy policy makers because the research literature has already been identified, selected, appraised, and synthesised in a systematic and transparent way. Additionally, a systematic review makes possible more constructive policy debates because stakeholders can focus on the synthesis and its local applicability rather than on which single study has greater credibility [3].

In order to make informed decisions, health-system policy makers need timely access to systematic reviews that can be easily retrieved using terminology that is understandable to them and that are presented in ways that facilitate rapid scanning for relevance, recency of searches for potentially relevant studies, the settings of studies included in the review, and quality of the review [3,4]. A systematic review of the factors that influence the use of research in policy making identified timing/timeliness as one of two factors that increased the prospects for research use among health-system policy makers [3,5]. However, when attempting to retrieve systematic reviews in a timely fashion, health-system policy makers typically cannot search all of the potential sources of systematic reviews. Moreover, policy makers typically cannot search most sources of systematic reviews, like The Cochrane Library, using terms with which they are familiar. The number and searchability of existing sources of systematic reviews become particularly frustrating when policy makers know there is likely to be a review available on a topical issue. Moreover, search results typically do not highlight the types of decision-relevant information that health-system policy makers are seeking [3,4].

One response to the similar types of issues faced by clinical decision makers has been the development of evidence services that provide regular email alerts about newly identified research products and a searchable database of these products[6]. However, no 'full-serve' evidence service currently exists to meet the needs of health-system policy makers. Existing evidence services that include health-system policy makers among their target audiences, such as E-watch (http://kuuc.chair.ulaval.ca/english/index.php) and CHAIN Canada (http://www.epoc.uottawa.ca/CHAINCanada/), do not focus on systematic reviews. Existing evidence services that focus on high-quality studies (not just systematic reviews), such as Evidence Updates (http://plus.mcmaster.ca/EvidenceUpdates/), do not target health-system policy makers[6].

To address this gap, we developed a full-serve evidence service for health-system policy makers. First, we developed Health Systems Evidence, which contains over 1,400 syntheses about governance, financial, and delivery arrangements within health systems and about implementation strategies relevant to health systems. By syntheses we mean both systematic reviews and two types of review-derived products, namely, policy briefs and overviews of systematic reviews [7]. A policy brief summarises how the findings from a number of systematic reviews pertain to a pressing problem, select options for addressing the problem, and key implementation considerations, whereas an overview provides a 'map' of all available systematic reviews on a broad health-system topic. The reviews have been (a) categorised by topic (*i.e.*, by health-system arrangement or implementation strategy), type of review (*i.e.*, policy brief, overview of reviews, Cochrane systematic review, systematic review, or systematic review protocol), and type of question addressed (*i.e.*, effectiveness, not effectiveness, and 'many'); (b) coded by the last year in which searches for studies were conducted and by the countries in which included studies were conducted; (c) rated for quality using the AMSTAR (A MeaSurement Tool for the 'Assessment of multiple systematic Reviews') instrument [8,9]; and (d) linked to available user-friendly summaries, scientific abstracts, and full-text reviews that are available free online [10].

Second, we identified systematic reviews in Health Systems Evidence that are neither available free online nor available through subscriptions held by the Ontario Ministry of Health and Long-Term Care (MOHLTC) and developed a mechanism to reimburse publishers for full-text downloads of these reviews.

Third, we developed the format for monthly email alerts, which (in tabular format) identifies new additions to Health Systems Evidence and describes the type of review, type of question addressed, health-system arrangement or implementation strategy addressed, and title of the review. A hypertext link for each review enables policy makers to view the availability of (and links to) user-friendly summaries, scientific abstracts, and the full-text review. A hypertext link to the online Health Systems Evidence webpage enables policy makers to view additional information about these same recent database additions, including the last year searched, quality rating, the countries in which included studies were conducted, and the complete citation. (Electronic newsletter width restrictions precluded having all fields presented in the monthly email alerts.)

Our goal is to evaluate whether (and how and why) a full-serve evidence service increases the use of synthesised research evidence by policy analysts and advisors in the MOHLTC as compared to a 'self-serve' evidence service. The full-serve evidence service comprises database access (an effort to facilitate policy makers' efforts to 'pull' in research when they need it), monthly email alerts about new additions to the database (a 'push' effort), and full-text article availability (an additional effort to facilitate pull). A systematic review found that simply providing information (in the form of clinical-practice guidelines) can change clinical behaviour,[11] which leaves us reasonably confident that we have the potential to achieve an increase in evidence use among health-system policy makers. Moreover, the results of a cluster randomised trial indicate that a full-serve evidence service increased practicing clinicians' utilisation of evidence-based information from a digital library [12].

## Methods/design

We will conduct this trial using a sequential explanatory mixed-methods design, [13] beginning with the randomised controlled trial (RCT) and then following up with a qualitative process study to explore the RCT findings in greater depth. For an initial two-month baseline period, all participants will receive the self-serve evidence service. For the following six-month period, the intervention group will receive the full-serve evidence service and the control group will continue to receive the self-serve evidence service. For a final two-month period, both groups will receive the full-serve evidence service. This protocol received ethics approval from the Hamilton Health Sciences/Faculty of Health Sciences Research Ethics Board at McMaster University (project number 10-267).

## RCT methods/design

### Study population and recruitment

To recruit participants who deal with health-systems issues on a regular basis, we will invite all policy analysts and policy advisors from one purposively selected division of the MOHLTC to participate in the RCT. All division staff members similarly face a relatively new expectation about obtaining training in finding and using research evidence (in the form of an indicator in annual performance reviews), as well as a new mandate for using the Ministry's 'Research Evidence Tool' for submissions that support decision making at the Ministry Management Committee and cabinet levels. Moreover, a trial endorsement letter will be signed by the Assistant Deputy Ministry responsible for this division. These contextual developments precede the launch of the trial and help to create a favourable climate for the use of research evidence among all potential trial participants.

Based on estimates provided to us in June 2009 by the MOHLTC, there are approximately 49 policy analysts (four are junior program and policy analysts) and 99 senior policy analysts in the division (n = 148). We do not yet have an accurate estimate of the number of policy advisors in the division; however, this group is likely to include roughly 20 people and all of them are likely to be senior policy advisors. By including all three levels of policy analysts and (if applicable) both levels of policy advisors, we will gather evidence from a diverse group that plays different roles in the policy-making process. For example, a policy analyst might conduct the initial, extensive 'workup' of an issue, whereas a senior policy advisor might write a short briefing note for the Minister.

Selecting this sample of policy analysts and advisors raises two applicability/generalisabilty issues. First, these RCT participants will differ in whether and when they received training on finding and using research evidence. Two of us ([name] and [name]) delivered a series of five one-day workshops for policy analysts and advisors at the MOHLTC between July 2008 and March 2009 (*i.e.*, 14 to 22 months before the trial will begin). We delivered five additional one-day workshops, one half-day workshop, and one half-day webinar for policy analysts and policy advisors, as well as one 1.5-hour workshop for more senior MOHLTC executives who set expectations for these staff, between January and March 2010 (*i.e.*, two to four months before the trial will begin). Given the division's expectation about training, we can assume that most RCT participants will have received the training. However, newly hired policy analysts and advisors may not have received the training, and others may not have been able to participate due to scheduling conflicts; those that have received the training will differ in the recency of the training. Second, these RCT participants will differ in their experience, which is somewhat related to their position (*i.e.*, level of policy analyst and level of policy advisor). To address each of these applicability/generalisability issues, we will stratify the randomisation based on past training and current position (see below).

### Intervention and control arms

We will conduct a two-arm RCT with a full-serve evidence service as the intervention arm and a self-serve version as the control arm. Participants allocated to the full-serve evidence service will receive the following:

• database (Health Systems Evidence) access (facilitating pull)

• monthly email alerts (push)

• full-text article availability (facilitating pull)

Participants allocated to the self-serve evidence service will receive only database access, which is already publicly available at http://www.healthsystemsevidence.org.

### Randomisation

Participants will be randomised using a stratified design. After completing the baseline questionnaire during the two-month baseline period, participants will be allocated to strata based on past workshop attendance (yes or no) and their position (policy analyst, senior policy analyst, or policy advisor). This two-layer stratification will produce six strata. Participants will be randomised after all those who consent to participate in the trial have completed the baseline questionnaire. We will assign a unique participant ID number to each participant and then provide the list of IDs to a biostatistician external to the research team who will conduct the randomisation and keep a log to provide a clear audit trail. The biostatistician will then communicate directly with a knowledge broker external to the research team who will be generating the email alerts and with the website server administrator at McMaster University who will be establishing which participants get access to which evidence service. The participants and investigators will be blinded to group assignment.

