### Outcomes

Measuring the impact of knowledge transfer and exchange (KTE) interventions, such as the evidence service proposed here, poses significant challenges [14]. The ultimate goal of KTE interventions is typically to improve health. However, there is a long chain of potential causal relationships between an evidence service and improved health. For instance, the evidence service may influence the use of research evidence in different stages of the policy-making process, which in turn may influence decisions made by patients and healthcare providers (*e.g.*, healthcare professionals, teams, and institutions), which may in turn influence whether cost-effective programs, services, and drugs get to the patients who need them and have their desired impacts, and which in turn may translate into improved health [15]. Moreover, even the first relationship in this long chain is complicated by the competing influences on the policy-making process, such as institutional constraints within a political system, stakeholder pressure campaigns, values and beliefs held by key decision makers, and external factors such as the state of the economy [16-18]. Similar challenges arise when assessing the impact of KTE interventions, such as guideline-dissemination strategies, on clinical practice and on health [19-21].

Given these challenges, our primary and secondary outcomes for the trial are proxy measures for the use of research evidence in policy making. The primary outcome will be a measure of utilisation that is similar to the one used in a trial of the McMaster Premium Literature Updating Service (PLUS) [12]. Specifically, we will track the mean number of site visits/month/participant across trial groups during each period, that is, the baseline period, intervention period, and crossover period. We will also provide related descriptive measures such as the proportion of users per month in each of the full-serve and self-serve groups; the frequency with which the full monthly update page, systematic review records, and the more detailed documentation for each review (*e.g.*, user-friendly summaries, scientific abstracts, and full-text reports) are accessed; the mean number of minutes per month that participants use the database (with a 'time out' set at 60 minutes); and the number of times the monthly email alerts are forwarded.

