Health Systems Evidence will be hosted on a secure server at McMaster University and will require a user login that will be used to accurately track their usage of the database. A user login is necessary because individuals from the MOHLTC do not have a consistent IP address when accessing external websites, which would preclude the collection of utilisation data if the site were hosted without requiring users to login. In addition, requiring user login will partially protect against contamination of the control group. However, we cannot rule out the possibility that individuals in the intervention arm of the study will forward monthly email alerts and full-text systematic reviews that are available only by subscription to individuals in the control arm; however, we will collect data about alert forwarding.

For the secondary outcome, we will use a survey based upon the theory of planned behaviour to measure participants' intention to use research evidence. The theory of planned behaviour is a model of how human action is guided [22,23], and it consists of three variables--attitudes (*i.e.*, beliefs and judgments), subjective norms (*i.e.*, normative beliefs and judgments about those beliefs), and perceived behavioural control (*i.e.*, the perceived ability to enact the behaviour)--that shape the behaviour intentions of people, which is in turn a strong predictor of future behaviour [23-25]. In Figure 1, we outline linkages among the intervention, contextual developments (described above), and theory of planned behaviour constructs and measures.

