### Data management and analysis

Data will be entered into SPSS 16.0 (IBM Corporation, Somers, NY) after all data collection has been completed. Analyses will be conducted by two members of the research team (SH and [name]), and during the analysis, neither they nor other study investigators will have access to the key linking the participants to their unique identifiers.

We will treat both outcome measures as continuous variables and analyse the change in these measures over time using a two-way mixed-effects linear repeated-measures analysis of variance (ANOVA), with the interaction of intervention by time as the main feature of interest. In addition, we will control for four variables--past workshop attendance, position (policy analyst, senior policy analyst, or senior policy advisor), branch within the division (of which there are six), and number of years working at the MOHLTC--using analysis of covariance. Given the likelihood that the distribution of the outcomes will be skewed, we will transform the data where necessary and possible, which may include adjusting the time period for which we calculate the mean number of site visits/participant (*e.g.*, calculating the mean over two months) if there are insufficient data for analysis. Moreover, as part of a secondary analysis, we will assess whether there is an interaction between each of these variables (entered as a fixed factor) and the outcome measures. We will also qualitatively compare the number of participants in the intervention and control groups that do not complete the follow-up survey and assess whether their baseline characteristics can help to explain their loss to follow-up.

For all analyses, we will use the intention-to-treat principle and report 95% confidence intervals; *p *values equal to or less than .05 (two-tailed) will be considered significant. For the primary outcome measure (mean number of site visits/month/participant), missing data are irrelevant because it is a naturalistic measure. For the secondary outcome measure (obtained through the survey), missing data can be taken into account through the use of a mixed-effects model.

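### Baseline visits are logged around the time of the single-batch randomisation, but neither the allocation nor the listed covariates use them, which costs precision and arm balance

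*Protocol article*

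**What the plan says.** All statements are in the Protocol article.

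- **Data before treatment differs.** Methods/design: "For an initial two-month baseline period, all participants will receive the self-serve evidence service". Outcomes: the site "will require a user login that will be used to accurately track their usage of the database", and the primary outcome is followed "during each period, that is, the baseline period, intervention period, and crossover period".
- **Allocation.** Randomisation: "participants will be allocated to strata based on past workshop attendance (yes or no) and their position", which makes six strata. On timing: "Participants will be randomised after all those who consent to participate in the trial have completed the baseline questionnaire". An external biostatistician receives a list of participant IDs and allocates them. Prior use of the site is not a factor.
- **Reason for the strata.** Study population and recruitment presents training and position as applicability issues. On training it adds that "we can assume that most RCT participants will have received the training", then lists exceptions such as new hires and scheduling conflicts.
- **Analysis.** Data management and analysis specifies a mixed-effects repeated-measures ANOVA with the intervention-by-time interaction as the feature of interest. It lists four covariates: workshop attendance, position, branch and years at the Ministry. Baseline visits are not among them. Skew is foreseen ("Given the likelihood that the distribution of the outcomes will be skewed"), and the response is transformation or a wider averaging window.

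**The concern.** The pre-treatment value of a primary outcome is usually among its best predictors. Here it costs nothing to obtain and is available, or nearly so, when the whole sample is allocated at once. The two chosen factors were not picked to predict site use, and one of them may separate few people because most are expected to have attended a workshop.

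If one arm by chance holds more of the frequent users, its baseline mean is high and is expected to fall back towards the overall mean. The interaction compares change over time between arms, so this fall enters the treatment estimate with a sign opposite to the baseline gap. The sample is fixed at one division, so recruitment cannot buy the lost precision back. Allocation happens once and cannot be repeated.

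**Working it through.** **1. The plan's own figures.** Inputs from Statistical precision and Data management and analysis: 74 per group, SD 1.0, 80% power, two-sided .05, six monthly follow-up points, ICC = r. The formula is

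d = (1.960 + 0.842) × sqrt{2[1 + 5r] / (6 × 74)}.

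It gives 0.266, 0.297, 0.352, 0.399 and 0.420 for r = .2, .3, .5, .7 and .8. These match the stated 0.27, 0.30, 0.35, 0.40 and 0.42. They are post-baseline, time-averaged differences that take no credit for baseline. With seven points the first two would be 0.258 and 0.291, which do not match.

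**2. Size of a chance baseline gap.** Assume the same correlation r between any two months, and take baseline as the mean of its two months. Then, in monthly SD units:

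- Var(baseline mean) = (1 + r)/2
- Var(six-month mean) = r + (1 − r)/6
- covariance = r
- slope of follow-up on baseline = 2r/(1 + r)
- SD of the arm gap at baseline = sqrt{(2/74)(1 + r)/2}

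**3. What reaches the change contrast.** A gap g shifts the change-from-baseline arm difference by −(1 − slope) × g. The per-person variance of the change is (2/3)(1 − r). The share due to the baseline gap is therefore

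(1 − slope)² × [(1 + r)/2] / [(2/3)(1 − r)] = 0.75(1 − r)/(1 + r).

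| | ICC .2 | ICC .5 | ICC .8 |
|---|---|---|---|
| SD of baseline gap | 0.127 | 0.142 | 0.156 |
| Slope | 0.333 | 0.667 | 0.889 |
| Shift of change contrast at a 1.96-SE gap (absolute) | 0.17 | 0.09 | 0.03 |
| Share of change-contrast variance | 50% | 25% | 8% |
| Stated detectable difference | 0.27 | 0.35 | 0.42 |
| Detectable difference, change contrast | 0.336 | 0.266 | 0.168 |
| Detectable difference, baseline as covariate | 0.238 | 0.230 | 0.161 |

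Example at ICC .2: 1.96 × (1 − 0.333) × 0.127 = 0.17. The last two rows use the same multiplier 2.802, with per-person variances (2/3)(1 − r) and Var(six-month mean) − r²/[(1 + r)/2]. The covariate lowers the SD of the estimate by 29%, 13% or 4% (for example 0.238/0.336 = 0.71).

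**4. Skewed counts.** This step simulates 148 people under assumptions: Poisson visits, lognormal personal rates with a mean of one visit a month, use unrelated to a simplified set of strata, no treatment effect and 3,000 runs per scenario. Sorted allocation randomises within strata in pairs ordered by baseline visits. The SE of the arm difference is:

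| Log-SD of rates, scale | Change, planned strata | Change, sorted pairs | Covariate, planned strata | Covariate, sorted pairs |
|---|---|---|---|---|
| 0.8, raw | 0.134 | 0.117 | 0.114 | 0.114 |
| 1.2, raw | 0.132 | 0.123 | 0.120 | 0.119 |
| 0.8, log | 0.061 | 0.050 | 0.051 | 0.050 |
| 1.2, log | 0.055 | 0.047 | 0.049 | 0.048 |

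Once the covariate is in, sorting adds almost nothing to precision. It does change balance. The SD of the baseline gap falls from 0.19 to 0.10 visits a month (log-SD 0.8) and from about 0.32 to 0.21 (log-SD 1.2). The chance that the 15 heaviest users split 10:5 or worse falls from about 25–28% to about 4–5%. The exact hypergeometric figure without sorting, for 15 heavy users among 148, is 27.6%.

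**The case against.** The case against is strong on several counts.

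- **The design is valid as written.** Chance imbalance in a variable left out of the strata is already covered by the standard error and the type I error rate. A reader might infer that the allocation biases or distorts the primary result. The documents do not support that. This stands in full.
- **The interaction already deals with much of it.** Baseline is a time point in the model, so a stable difference between arms cancels. This stands, but regression to the mean does not cancel, and step 3 measures only that remainder.
- **A raw baseline gap is not an effect-sized error.** In baseline SDs the gap has an SD of sqrt(2/74) = 0.164, so its 95% range is about ±0.32. It is tempting to set this beside the detectable 0.27 to 0.42. The gap does not pass one-for-one into the planned contrast; the shift is 0.17 down to 0.03 SD.
- **The gain is mostly an analysis matter.** The covariate gives nearly the same precision under either allocation. This stands and sets the order of the fix.
- **The text does not show that a few heavy users dominate.** It says only that skew is likely. It also foresees sparse monthly data, and with many ties at zero, sorting would achieve little.
- **Logs may be incomplete at allocation.** Randomisation is tied to questionnaire completion, not to the end of the baseline period. This stands, and the fix has to settle it.

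What survives is that the article fixes its strata and names its covariates, and a recorded baseline value of the primary outcome is in neither list.

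**Conclusion.** The point holds as an avoidable loss of precision and balance, not as an error that invalidates the trial. At ICC .2 half the variance of the change-from-baseline arm difference comes from the chance baseline gap. At ICC .5 it is a quarter, and at ICC .8 it is 8%, where the matter is minor. The article says that it could not estimate the ICC, so the whole range remains open. The 29% reduction in SD at ICC .2 is the most favourable end. In the skewed no-effect simulations the covariate lowered the SE by 9% to 16%.

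It would be wrong to restate this as a rise above the planned 80% power. The plan's figures belong to a post-baseline average, not to a change contrast.

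The results rest on these assumptions: equal correlation between months, a two-month baseline mean, the interaction read as a change-from-baseline contrast, and, for step 4, an assumed visit distribution. The article gives no such distribution, so the number of heavy users and the degree of skew are assumptions.

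**What to change.** 1. **Analysis (most of the gain).** Enter each participant's logged baseline visits as a covariate in the primary model, transformed in the same way as the outcome, and let the post-baseline months of the intervention period be the outcome. This adds one sentence to Data management and analysis.
2. **Allocation (mainly balance and robustness to skew).** State that randomisation takes place at the end of the baseline period. Within each of the six strata, sort the IDs by logged baseline visits and randomise in consecutive blocks of two. The number of strata does not change, so no small cells are added. The external biostatistician needs one more column, from the server log, and concealment is unaffected. Once the covariate is in the model, expect about 0–4% extra precision, and little benefit if many participants tie at zero.

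The costs are small. Allocation must wait for nearly complete baseline logs. If part 2 is adopted, part 1 must be too, because without baseline visits in the model the standard error would not reflect the balanced allocation and would be somewhat too wide.

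### Participants cannot be blinded as the protocol states, and the stated analysis safeguard hides identity rather than arm

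*Protocol article*

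**What the plan says.** The Randomisation section of the protocol article states: "The participants and investigators will be blinded to group assignment". It gives no qualification and no end point. The same section describes how allocation is handled. A biostatistician outside the research team randomises a list of IDs and keeps the log, then deals directly with an outside knowledge broker, who produces the alerts, and with the server administrator, who sets access.

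The Methods/design section describes what participants experience: "For an initial two-month baseline period, all participants will receive the self-serve evidence service". For the next six months "the intervention group will receive the full-serve evidence service and the control group will continue to receive the self-serve evidence service". Under Intervention and control arms, full-serve adds monthly email alerts and full-text availability to the database, whereas "Participants allocated to the self-serve evidence service will receive only database access".

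The Outcomes section makes server-logged site visits the primary outcome and a survey of intention to use research evidence the secondary outcome. The descriptive usage measures include "the number of times the monthly email alerts are forwarded".

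The RCT Data management and analysis section says of the two analysts that "neither they nor other study investigators will have access to the key linking the participants to their unique identifiers". It also allows the data to be transformed where needed, and the period over which mean visits are calculated to be changed if data are sparse.

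**The concern.** A protocol that claims blinding tells readers they may discount differences caused by people knowing what they received. Here the arms differ in something the recipient sees each month, so the claim looks untrue for participants. That matters most for the intention survey, which is answered at the end of the six months. It also matters for the item on perceived usefulness that was added to the instrument. Staff who know they have been given the enhanced service may report stronger intention for that reason alone.

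A second question concerns the analysts. If they can tell which group is which while the scale and averaging window of an outcome are undecided, those choices can be influenced, even unintentionally, by how the result looks.

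**Working it through.** The point is one of consistency, so no arithmetic decides it. The only statistical figures in the protocol are the detectable differences for site visits under Statistical precision, and they are sound. With 74 per group, six follow-up points, 80% power and two-sided .05, d = (1.960 + 0.842) × √[2(1 + 5·ICC)/(74 × 6)]. This gives 0.266, 0.297, 0.352, 0.399 and 0.420 for ICCs of .2, .3, .5, .7 and .8, against the stated 0.27, 0.30, 0.35, 0.40 and 0.42. They neither depend on blinding nor measure what its absence would do.

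**Participants**
1. Months 1–2: all have self-serve, with no alerts.
2. Months 3–8: one arm receives a monthly email and added full-text access. The other arm sees no change, and no sham email or dummy feature is described.
3. A person who starts to get a monthly email after two months without one can see that their service has changed.
4. The Outcomes and Discussion sections accept that full-serve staff may pass alerts and articles to colleagues in the control arm. That would show some controls what they are not receiving.
5. Participants therefore cannot be blinded as described. At most they could be kept unaware of which version is under test, and the protocol does not claim this.

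**Investigators during conduct**

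Allocation and delivery pass through people outside the research team or through the server administrator, and data are entered only after collection is complete. This is a workable shield.

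**Analysts**
1. The item withheld is the key from person to ID. It hides who someone is, not which arm they are in.
2. The main term in the model is intervention by time, so the analysis file needs an arm variable. The article does not say whether it is masked.
3. Suppose it is coded A/B. In months 3–8 alerts go to one arm only, so recorded forwarding originates with that arm and shows which code is full-serve.
4. The Background section describes a mechanism that reimburses publishers for reviews neither free online nor covered by Ministry subscriptions. If those downloads are logged separately, they are a second marker.
5. Visits to the monthly update page are likely to differ by arm, because the alerts link there, although the protocol does not say that controls are excluded from it.
6. The transformation and averaging window may still be undecided when these variables are in hand.

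**Exposure by outcome**

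| Outcome | How recorded | Open to reporting bias? |
|---|---|---|
| Site visits (primary) | Server log through user login | No |
| Intention (secondary) | Self-completed survey | Yes, all participants |

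**The case against.** The best defence is that the blinding has real substance for investigators. A reader might infer that none of the stated blinding exists. The document does not support that, since external randomisation and delivery can keep investigators unaware of allocation throughout conduct. This part of the defence stands.

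A reader might also infer that any full-text download before the final two months must come from the full-serve arm. That is wrong. The database links to reviews that are free online, the Ministry holds subscriptions to others, and controls have the database. Only reimbursed downloads are specific to the arm, and nothing says they are logged separately. Likewise, a zero forwarding count does not identify an individual control, and a site-visit count alone does not reveal arm. All of this stands. It does not rescue A/B masking, because one forwarded alert in the intervention period is enough to label the group.

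A third defence is that arm coding and the order of data release are details an article may leave to a fuller document, and that the Randomisation section already blinds investigators, a group that includes the analysts. This stands in part: it would go too far to say that the analysts are known to receive unmasked arms. But the one safeguard the article does describe does not do what the blinding sentence promises. The statement about participants is not an omitted detail at all; the design contradicts it.

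Finally, the primary outcome is free of reporting bias, and the exposed outcome is secondary and acknowledged to be a proxy. That is true, and it limits the consequence.

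**Conclusion.** The concern holds, within limits. Participants cannot be blinded as the protocol says, so the intention outcome is unblinded self-report for everyone randomised (at least 148 people on the planning figure). For investigators, the arrangements during conduct are adequate. The weakness is at analysis, where the stated safeguard masks identity only and the usage data would reveal the full-serve group while analytic choices remain open.

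The size of any reporting bias cannot be derived from the document, and a figure in SD units would be pure assumption, so none is given. Logged site visits are not exposed to reporting bias.

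The conclusion assumes that no sham alert exists beyond what is described, and that forwarding counts reach the analysts with the other usage data. What participants are told about the two arms at consent cannot be checked here. It could affect how they interpret their service, but not whether they notice the alerts.

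**What to change.** 1. Replace the blinding sentence with one that says who is masked, to what and until when: participants are not blinded; investigators and analysts are masked to arm until the analyses are locked.
2. State that the intention result, and the usefulness item with it, is unblinded self-report to be interpreted with that caution.
3. Give the analysts arms coded A/B.
4. Withhold the arm code and the arm-revealing variables (alert forwarding, access to the monthly update page, reimbursed full-text downloads) until the transformation and time window are fixed and both the site-visit and the intention models have been run and locked. Releasing the code after the site-visit model alone would leave the intention analysis unmasked.

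The external biostatistician already keeps the randomisation log and could hold the code and these variables, though this would be an added duty. The cost is revised wording, a two-step data release and a short delay before the descriptive usage tables. Coding has one limit: a large difference in visits may itself suggest which arm is which, and this is why the transformation and window should be settled first.
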